## **2. SECONDARY ANALYSES**

The secondary efficacy analyses will be based on one-way analysis of covariance (ANCOVA) with post-hoc Bonferroni correction for intergroup comparisons. The ANCOVA model is used to analyze the effect of brace weaning protocols on the outcomes of changes of major curve Cobb angles and truncal balance as well as HRQoL measures, whilst adjusting for baseline covariates. Baseline covariates will be identified through testing the relationships of baseline parameters including socio-demographics, body size, maturity parameters, and other baseline radiographic measurements with the study outcomes using correlation tests.

The comparison between groups will be carried out using the adjusted mean

difference between the study groups at all post-weaning time points. The estimated difference between the two weaning protocols will be displayed along with the associated 95% confidence interval and p-value. The analysis will be carried out according to intention-to-treat (ITT) and PP principle.

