## **Supplementary 2 Statistical Plan**

### **TITLE: A RANDOMIZED CONTROLLED TRIAL COMPARING GRADUAL AND IMMEDIATE BRACE WEANING FOR CLINICAL MANAGEMENT OF ADOLESCENT IDIOPATHIC SCOLIOSIS PATIENTS**

#### **DATA PROCESSING AND ANALYSIS**

##### **1. SAMPLE SIZE CALCULATION**

The sample size of this clinical trial will be determined based on an independent sample *t*-test to detect a difference between the two groups (immediate and gradual bracing weaning) for the changes in Cobb angle. According to a previous study [1], the average increase in Cobb angle at 1 year after brace weaning was 3.5 degrees. Curve progression is observed in 43.5% of patients. At 2 years, the curve progression rate was 46.5% with an average increase of major curve Cobb angle of 5.1 degrees. Based on this result, we consider a difference of 2 degrees between the changes in Cobb angle as clinically relevant, with an equivalence margin of 0.4. Assuming a standard deviation of 6 degrees for the Cobb angle change, a sample of 128 per group is required to detect the difference of the statistical test with 80% power at a 0.05 level of significance. Accounting for 20% overall attrition rate at 1 year follow-up, we will recruit 308 AIS patients (154 in each group) for this prospective study.

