##### **2. STUDY OUTCOMES**

Primary outcome was the change in major curve Cobb angle from baseline to 6-month, 12-month, and 24-month follow-up. Curve progression was examined as  $>5^\circ$  increase of major Cobb angle between follow-up time points and baseline. Secondary outcomes were the change in truncal balance in truncal shift and listing (C7-central sacral vertebral line deviation) from baseline to 6-month, 12-month and 24-month follow-up.

Secondary outcomes also included the refined Scoliosis Research Society 22-item (SRS-22r) questionnaire total score, the EuroQol-5-dimension (EQ-5D) utility score and EuroQol-visual analogue scale (EQ-VAS) at all post-weaning time points.

All study outcome measures were studied at baseline (the time of weaning), post-weaning 6, 12 and 24 months.

Body weight, standing and sitting body height, arm span, and HRQoL measures were measured, and curve type (i.e. thoracic, thoracolumbar/ lumbar) and coronal Cobb angle were assessed from whole spine standing posteroanterior and lateral radiographs taken simultaneously at each visit as per clinical routine. Skeletal maturity was routinely determined at the time of weaning using Risser staging, distal radius and ulna (DRU) classification and Sanders staging. In addition to Cobb angle and truncanl balance, other radiological parameters including T1 tilt, shoulder height, sagittal vertical axis (SVA), thoracic kyphosis (T5-12) and lumbar lordosis (L1-S1) were measured by two assessors independently. An intra-class correlation coefficient (ICC) with 95% confidence interval will be used to estimate the inter-assessor reliability.

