### 1. PRIMARY ANALYSIS

The primary analysis will be evaluated by two independent sample *t*-test to determine the significance of the differences in change of Cobb angle and truncanl balance

between the two groups. The analysis will primarily be carried out according to intention-to-treat (ITT) and subordinately based on per-protocol (PP) principle. The ITT analysis will include any randomized patients with non-missing efficacy measures. The PP analysis will include all randomized patients in ITT who fulfil the criteria of PP population.

The PP population is defined as a subset of the ITT population. Patients will be included in the PP population if they have:

- no late report violations of entry criteria,
- no incorrect treatment group assigned,
- no major protocol deviation(s) that is/are clinically significant to efficacy outcome,
- no treatment during follow-up after weaning, and
- with sufficient treatment compliance.

Sufficient treatment compliance is defined as gradual brace weaning patients having completed at least 8 hours/night of brace-wear for >80% of the 6-month gradual weaning period. Brace-wear compliance (hours/day) for the 6-month gradual weaning period will be recorded by thermal sensor.

Both ITT and PP results will be reported for primary analyse.

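### The primary t-test on Cobb change is valid but not adjusted for baseline Cobb angle, and the secondary ANCOVA picks its covariates from the outcome data with no requirement to include the outcome's own baseline value

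*Supplement*

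**What the plan says.** **Primary model.** SAP, Statistical Analysis, 1. Primary Analysis, uses a two-independent-sample t-test "to determine the significance of the differences in change of Cobb angle" and truncal balance, by ITT first and per protocol second. No covariate is named. SAP section 2, Study Outcomes, defines the outcome: "Primary outcome was the change in major curve Cobb angle from baseline to 6-month, 12-month, and 24-month follow-up". The final protocol (3c, Study Duration) places the primary end point at 1 year. The sample size rests on the same unadjusted test, "to detect a difference between the two groups (immediate and gradual bracing weaning) for the changes in Cobb angle".

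**Design.** Eligibility admits primary curves of 20 to 40 degrees (final protocol, section 4, Inclusion Criteria). Section 5, Randomization and Allocation, describes blocks of random even size and mentions no stratification factor.

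**Adjusted model.** SAP, 2. Secondary Analyses, plans an ANCOVA of Cobb change, truncal balance change and HRQoL at all post-weaning visits, in ITT and per-protocol populations. The covariates are found as follows: "Baseline covariates will be identified through testing the relationships of baseline parameters including socio-demographics, body size, maturity parameters, and other baseline radiographic measurements", tested for correlation with the study outcomes. The section gives no final list, significance threshold or forced term.

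**HRQoL outcomes.** The protocol's Secondary outcomes and SAP section 2 list SRS-22r total and EQ-5D utility as scores at follow-up, not as changes. All outcome measures are also taken at baseline.

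**The concern.** Subtracting the baseline fixes its coefficient at one instead of estimating it. If change still depends on starting curve size, the change-score t-test leaves that part of the variation in the error term, and nothing in the described randomisation balances it. The protocol's introduction itself treats curve size as prognostic: it cites continued progression for curves of 40 degrees or more at maturity. Baseline Cobb is measured in every patient, so the information is already there.

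The planned ANCOVA could recover it, but only if baseline Cobb is selected. The candidate list speaks of other baseline radiographic measurements, which leaves unclear whether baseline Cobb is a candidate at all. Because selection uses the outcome data and has no stated threshold, two analysts following the SAP could report different adjusted estimates.

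For SRS-22r and EQ-5D, baseline is not even subtracted. The listed candidate classes do not name baseline HRQoL, and although the list is introduced as non-exhaustive, nothing requires it.

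**Working it through.** **Inputs from the SAP, Sample Size Calculation.** The difference: "we consider a difference of 2 degrees between the changes in Cobb angle as clinically relevant". The spread: "Assuming a standard deviation of 6 degrees for the Cobb angle change". Power is 80%, alpha 0.05, 128 per group, and 154 per group after allowing for 20% attrition. Sidedness is not stated; two-sided is assumed here.

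**Plan's own figure.** n per group = 2(1.960 + 0.842)² × 6² / 2² = 141.3, so 142 (143 by the noncentral t). The stated 128 is not reproduced. The SAP also adds "with an equivalence margin of 0.4" without explaining its unit or role; variants using it give 78, 99, 174 or 221, and equivalence-test variants give 108, 155 or 241. A one-sided test needs 112. The 154 equals 128 × 1.2 = 153.6, rounded up. After 20% loss, 154 × 0.8 = 123.2, so about 123 per group are analysed.

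**Effect of adjustment.** Let r be the correlation between baseline Cobb and Cobb change. The documents do not give it, so a range is shown. Residual SD = 6√(1 − r²). The equivalent gain in sample is 1/(1 − r²) − 1. Power is for 2 degrees, two-sided 0.05, noncentral t, 123 per group.

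| \|r\| | Residual SD | SE reduction | Equivalent gain in patients | Power |
|---|---|---|---|---|
| 0 | 6.00 | 0% | 0% | 74.0% |
| 0.1 | 5.97 | 0.5% | 1% | 74.4% |
| 0.2 | 5.88 | 2.0% | 4% | 75.7% |
| 0.3 | 5.72 | 4.6% | 10% | 77.9% |
| 0.4 | 5.50 | 8.3% | 19% | 81.1% |

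At 123 per group, 80% power needs a residual SD of about 5.58, since 2/5.58 = 0.359 is the detectable standardised difference. Then r = √(1 − (5.58/6)²), about 0.37. The normal approximation gives 0.36.

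**How much imbalance passes through.** For illustration, assume baseline is uniform on 20 to 40 degrees and r = 0.3.
- Baseline SD = 20/√12 = 5.77.
- Slope of change on baseline = 0.3 × 6/5.77 = 0.31.
- SE of the chance imbalance = 5.77 × √(2/123) = 0.74 degrees.
- Contribution to the estimate = 0.31 × 0.74 = 0.23 degrees, against a total SE of 6 × √(2/123) = 0.77, which already includes it.

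**Type I error of the selection step.** Two simulations, entry at p < 0.05:
- 15 independent candidates, 128 per group, 4,000 runs: 4.5% to 4.9% with selection, against 4.6% to 4.9% for the t-test and 4.4% to 4.9% for a pre-specified ANCOVA.
- 20 to 30 null candidates, 123 per group, 3,000 runs: 4.8% to 5.0%.

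Neither shows inflation. Both model a mechanical rule applied to the pooled arms; neither covers discretionary choice.

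**The case against.** The strongest reply is that nothing here is an error. The outcome is change from baseline, so baseline is not ignored. Under randomisation the t-test is unbiased, its standard error already allows for chance imbalance, and it matches the test used for the sample size. The criticised selection affects only secondary analyses, and an adjusted analysis with confidence intervals is already planned. All of that stands, and it makes this a point about efficiency and pre-specification rather than validity.

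It also stands that the gain may be small. The 20 to 40 degree entry range limits baseline spread, and at |r| of 0.1 to 0.2 power rises by only 0.4 to 1.7 points.

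Four stronger readings are tempting, and the documents do not support them:
- **That baseline imbalance passes undiluted into the primary estimate.** Only slope times imbalance remains after subtraction.
- **That covariates will be selected separately for each outcome and visit.** The SAP does not say so; its wording merely leaves this open.
- **That outcome-driven selection inflates type I error.** Neither simulation found this for a mechanical rule.
- **That adjustment repairs the power shortfall.** That shortfall comes from the sample-size arithmetic and a two-sided reading. One-sided, unadjusted power at 123 per group is about 83%.

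The objection does not answer the missing covariate list, or the absence of any requirement to adjust follow-up HRQoL scores for their baseline.

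**Conclusion.** The point holds as a low-cost improvement. The primary test is sound but not adjusted for a covariate available in everyone. The adjusted analysis is not reproducible from the SAP text, and it may omit the one covariate most worth having.

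In large samples, adjusting for baseline gives precision equal to or better than the change-score t-test. The gain at 123 per group runs from nil at r = 0 to 7.1 power points (81.1 − 74.0) at |r| = 0.4. This rests on the SAP's difference of 2 and SD of 6, a two-sided 5% test, 20% loss from 154 per group, and an assumed r. It should not be counted on to restore 80% power, and the sample-size calculation needs separate attention. The harm from correlation-test selection is analyst discretion and possible omission of the baseline value.

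**What to change.** In the SAP, before outcome data are analysed:

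1. Make the primary 12-month analysis an ANCOVA of Cobb change on arm and baseline major-curve Cobb angle. Curve type may be added if named in advance. Risser stage has little to offer, since eligibility already restricts it to stage 4 or above.
2. Keep the unadjusted t-test as a sensitivity analysis.
3. Adjust each secondary outcome, including SRS-22r, EQ-5D and EQ-VAS, for its own baseline value. Use the same pre-stated covariates at every visit and in both ITT and per-protocol populations.
4. Delete the selection of covariates by correlation tests.

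The cost is SAP wording and about one degree of freedom of the 244 (2 × 123 − 2) that the t-test has. The protocol and SAP already schedule every variable named, so no new data collection is needed.

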#### **b. Secondary outcomes**

- Change in truncal balance from baseline to 6 months, 1 year and 2 years follow-up.
- SRS-22r total score at 6 months, 1 year and 2 years follow-up.
- EQ-5D utility score at 6 months, 1 year and 2-years follow-up.

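### The SAP neither names nor guarantees each HRQoL instrument's own baseline score as a covariate in the HRQoL ANCOVA

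*Supplement*

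**What the plan says.** The final protocol's secondary outcomes (section 6) list "SRS-22r total score at 6 months, 1 year and 2 years follow-up" and "EQ-5D utility score at 6 months, 1 year and 2-years follow-up". Beside them stands "Change in truncal balance from baseline to 6 months, 1 year and 2 years follow-up". Truncal balance is thus a change, while the questionnaires are scores at a visit. SAP section 2, Study Outcomes, keeps this split and adds EQ-VAS, giving the "questionnaire total score, the EuroQol-5-dimension (EQ-5D) utility score and EuroQol-visual analogue scale (EQ-VAS) at all post-weaning time points". The same section plans the baseline values: "All study outcome measures were studied at baseline (the time of weaning), post-weaning 6, 12 and 24 months".

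The SAP's Secondary Analyses section describes the only HRQoL model, an ANCOVA for "outcomes of changes of major curve Cobb angles and truncal balance as well as HRQoL measures, whilst adjusting for baseline covariates". The covariates are to be identified by testing the relationships of "baseline parameters including socio-demographics, body size, maturity parameters, and other baseline radiographic measurements with the study outcomes using correlation tests". The SAP gives no threshold for these tests and does not say whether they are run separately by outcome or by visit.

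**The concern.** HRQoL is the second of the two secondary aims, with a directional hypothesis in favour of gradual weaning. When a questionnaire is given before and after, the earlier score is the obvious covariate for the later one. Here it is collected in the ordinary course of the trial, yet the plan does not commit to using it. The named covariate groups follow the protocol's own measurement headings (socio-demographics, body size and maturity, scoliosis-specific radiographic parameters). The separate HRQoL heading is not carried over.

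If the baseline score stays out, differences between patients that were already present at weaning remain in the error term, and a chance difference between the arms at weaning is partly carried into the follow-up comparison. Whether it goes in is left to whoever runs the screen.

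**Working it through.** **The plan's own figures.** The documents give no figure for HRQoL: no SD, no target difference, no correlation. The only sample size is for Cobb change, set "with 80% power at a 0.05 level of significance". Taken two-sided, 2 × (1.960 + 0.842)² × 6² / 2² = 141.3, so 142 per group against the stated 128. That is a separate matter and does not bear on this point. The figures used here are the 154 per group and the 20% attrition at 1 year: 154 × 0.8 = 123 evaluable per group.

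**Assumptions.** Two-sided 5% level (sidedness is not stated), HRQoL in SD units, equal variances at baseline and follow-up, and r between 0.3 and 0.8.

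**Formulas.**
- Residual variance after adjusting for the baseline score: 1 − r². Standard error and interval width scale by √(1 − r²).
- Difference detectable with 80% power: (1.960 + 0.842) × √(2(1 − r²)/123).
- Power for an illustrative true difference of 0.3 SD: Φ(0.3/√(2(1 − r²)/123) − 1.960).
- Part of a chance baseline difference d carried into an unadjusted follow-up comparison: r × d, shown for d = 0.2 SD.

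| r | Residual variance | Width factor | Detectable difference (SD) | Power at 0.3 SD | Carried over, unadjusted (SD) |
|---|---|---|---|---|---|
| not adjusted | 1.00 | 1.000 | 0.357 | 65% | – |
| 0.3 | 0.91 | 0.954 | 0.341 | 69% | 0.06 |
| 0.5 | 0.75 | 0.866 | 0.309 | 78% | 0.10 |
| 0.7 | 0.51 | 0.714 | 0.255 | 91% | 0.14 |
| 0.8 | 0.36 | 0.600 | 0.214 | 98% | 0.16 |

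**How large a chance imbalance is plausible.** Its standard error is √(2/123) = 0.128 SD, so the 95% range is about ±0.25 SD. A difference of 0.2 SD is 0.2/0.128 ≈ 1.6 standard errors: possible, but on the large side.

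**If HRQoL were analysed as change.** A change score has variance 2(1 − r), against 1 − r² for ANCOVA: 1.40 against 0.91 at r = 0.3, 1.00 against 0.75 at 0.5, 0.60 against 0.51 at 0.7, and 0.40 against 0.36 at 0.8. Adjusting for baseline is the more precise choice throughout this range.

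**The case against.** A reader might infer that the plan leaves baseline HRQoL out altogether. The documents do not support that. The word *including* introduces examples, and the weaning questionnaire is a baseline measure, so it may be tested. If it is tested, it will very probably be picked. With 246 patients and an assumed 5% threshold, a correlation above roughly 1.96/√246 = 0.125 is significant, well below the range assumed here. The sentence on the ANCOVA outcomes can also be read as covering *changes* in HRQoL, which would use baseline by subtraction. Both readings are available. What stands is that neither is a commitment: the first depends on someone choosing to test the score, and the second conflicts with the endpoint definitions in the protocol and SAP.

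A reader might also call the endpoint definition faulty. It is not. A follow-up score is a sound ANCOVA outcome, and subtraction is no safeguard in itself: below r = 0.5 a change score is noisier than the raw follow-up score.

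Nor does a chance imbalance pass in full into the result, or bias it. Under randomisation the unadjusted comparison is unbiased, its confidence interval allows for chance imbalance, and only r times the difference is carried over.

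Finally, selecting covariates by correlation test affects every ANCOVA outcome; no outcome has its own baseline fixed. That is correct. For HRQoL the gap is plainer, because no named group would contain the baseline score and the endpoint is not defined as a change.

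**Conclusion.** The point holds as a gap in prespecification: each instrument's baseline score is collected at weaning but is neither named nor guaranteed as a covariate. The cost is precision and protection against chance imbalance, not validity, and it falls on secondary endpoints only. The primary Cobb comparison is untouched.

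The size depends on r, which the documents do not give. At r = 0.3 the gain is small (9% of variance, about 5% of interval width). At 0.5 to 0.7 it is 25% to 49% of variance and 13% to 29% of width. At 0.8 it is 64% and 40%. These figures compare adjustment with none. Any selected covariate that itself predicts HRQoL would take up part of the gain, and if the screen did admit the baseline score there would be nothing left to gain in precision, only a data-driven choice to remove. The change is worth making because it is nearly free and helps whether HRQoL is read as a score or as a change.

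**What to change.** In the SAP's Secondary Analyses section, state that each HRQoL ANCOVA models the follow-up score with the baseline value of the same instrument as a fixed covariate, whatever the correlation tests show: SRS-22r total on baseline SRS-22r total, EQ-5D utility on baseline utility, EQ-VAS on baseline EQ-VAS. This also settles whether HRQoL enters as score or change. The endpoint wording in the protocol's secondary outcomes and in SAP section 2 can stay.

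The cost is one sentence, with no new data, because the measures are already planned at weaning. Since the SAP imputes nothing, a patient without a weaning questionnaire would drop out of that model; the number so lost should be reported.

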### **3. SUBGROUP ANALYSES**

In subgroup analysis, number of patients with curve progression since brace weaning ( $>5^\circ$  increase of major Cobb angle) at post-weaning 24 months in the PP population will be reported with percentages. Multivariable logistic regressions were used to examine specifically whether brace weaning protocol (immediate/gradual), skeletal maturity status at weaning (Risser staging, DRU grades and Sanders stages) and any significant baseline parameters were associating factors for curve progression.

Pearson's Chi-square test was used to compare the occurrence of progression/non-progression/rebound (with  $>5^\circ$  increase of major Cobb angle at follow-up but major Cobb angle at weaning was less than prebrace major Cobb angle) between weaning protocol.

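### The 24-month count of curve progression is specified only in the per-protocol set, with no intention-to-treat analysis, and its progression and rebound classes overlap as written

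*Supplement*

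**What the plan says.** SAP, 2. Study outcomes, treats progression in the same paragraph as the primary outcome, as a more than 5-degree "increase of major Cobb angle between follow-up time points and baseline". SAP, 3. Subgroup analyses, then schedules the count and percentage "at post-weaning 24 months in the PP population will be reported with percentages". Two tests follow in that section: a multivariable logistic regression with weaning protocol among the factors, and "Pearson's Chi-square test was used to compare the occurrence of progression/non-progression/rebound" between the protocols. Neither sentence names an analysis set.

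SAP, 1. Primary analysis, builds the PP set from the ITT set. Two of its conditions matter here. One is "no treatment during follow-up after weaning". The other is compliance: "Sufficient treatment compliance is defined as gradual brace weaning patients having completed at least 8 hours/night of brace-wear" on more than 80% of the six-month weaning period. No compliance criterion is given for the immediate arm, and the final protocol (section 6, item 5) plans thermal sensors for the gradual arm only.

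Rebound is a more than 5-degree increase at follow-up, "but major Cobb angle at weaning was less than prebrace major Cobb angle".

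By contrast, the t-test on Cobb change is ITT first and PP second (SAP, 1. Primary analysis), and the ANCOVA uses both sets (SAP, 2. Secondary analyses).

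**The concern.** Progression is the yes/no form of the primary variable and the form in which the SAP cites its background rates (43.5% at 1 year, 46.5% at 2 years). It is the one form of that variable with no stated analysis of patients as randomised.

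Both PP conditions act after randomisation. Treatment after weaning may follow from progression, so removing treated patients may remove some of the events being counted. The wear-time rule selects patients in one arm with no counterpart in the other. If poor wearers differ in prognosis, the retained gradual-arm patients are no longer comparable with the immediate arm.

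The rebound definition is a separate fault. A contingency table needs each patient in one class, but every rebound patient as defined is also a progression patient. The percentage reported as progression, and the chi-square result, then depend on a coding choice that the plan does not state.

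**Working it through.** The plan gives no sample size or power for progression, so there is no stated figure to reproduce. The steps below first compare the texts, then show how much the choices could matter under stated assumptions.

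**1. Analysis sets, side by side**

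| Analysis | Set stated in the SAP |
|---|---|
| t-test, Cobb change and truncal balance | ITT, then PP |
| ANCOVA, Cobb change, truncal balance, HRQoL | ITT and PP |
| Progression count, 24 months | PP |
| Logistic regression | none named |
| Chi-square, three classes | none named |

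**2. One-arm compliance rule.** Inputs from the SAP: progression p = 0.465 (2-year rate in the previous study), 154 randomised per arm, 20% attrition (stated for 1 year, applied here to 24 months as an assumption), so 154 × 0.8 ≈ 123 evaluable. Assumed: no true effect, a share c of the gradual arm excluded, and excluded patients having r times the compliers' risk. The retained gradual-arm rate is p / [(1 − c) + c·r]; the immediate arm stays at 46.5%.

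Example, c = 0.3 and r = 1.5: 0.465 / (0.7 + 0.45) = 0.404, a difference of −6.1 points. Standard error = √(0.404 × 0.596 / 86.1 + 0.465 × 0.535 / 123) = 0.069, and the nominal two-sided 5% error becomes about 14.1%.

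| r | PP gradual-arm rate, c = 0.1 to 0.4 | Error rate |
|---|---|---|
| 1.0 | 46.5% throughout | 5% |
| 1.25 | 45.4% to 42.3% | 5.3% to 8.9% |
| 1.5 | 44.3% to 38.7% | 6.3% to 18.8% |
| 2.0 | 42.3% to 33.2% | 10% to 47% |

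With r below 1 the shift reverses. The documents give neither c nor r.

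**3. Exclusion for treatment after weaning.** If a share q of progressors is removed, the PP rate is p(1 − q) / (1 − pq).
- q = 0.1: 0.4185 / 0.9535 = 43.9%.
- q = 0.3: 0.3255 / 0.8605 = 37.8%.

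Equal removal in both arms gives no difference under no true effect. Removal of 30% in one arm and 10% in the other gives about 6 points, in either direction.

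With a true effect, assume 24-month changes that are normal with means 5.1 and 3.1 degrees (the SAP's 2-year mean and its 2-degree difference) and SD 6, and assume that treated patients are those above 10 degrees in both arms:

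| Share above 10 degrees removed | Progression, immediate vs gradual | Difference | Ratio |
|---|---|---|---|
| none | 50.7% vs 37.6% | 13.1 points | 1.35 |
| half | 45.0% vs 33.4% | 11.6 points | 1.35 |
| all | 37.8% vs 28.7% | 9.1 points | 1.32 |

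Under this equal rule the absolute rates fall clearly, the difference shrinks moderately, and the ratio barely moves.

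**4. Classes.** Take prebrace 32, weaning 30, follow-up 36 degrees. The increase is 6, so the patient is a progression case. Weaning (30) is below prebrace (32), so the patient is also a rebound case, although the final angle is 4 degrees worse than before bracing. The rule never sets the follow-up angle against the prebrace angle.

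If rebound made up an assumed 25% to 75% of a 46.5% rate, taking it out would leave a progression class of 0.465 × 0.75 = 34.9% down to 0.465 × 0.25 = 11.6%.

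For scale, simulate the change as normal (5.1, SD 6) and prebrace minus weaning angle as normal with assumed mean 0, 2 or 4 and SD 5. Then 90%, 85% and 78% of rebound cases end above their prebrace angle.

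**5. Data.** The final protocol's section 6 (items 3 and 4) and Table 1 do not list the prebrace Cobb angle, which any rebound rule needs.

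**The case against.** The strongest reply has four parts.

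**The randomised comparison exists elsewhere.** Progression dichotomises Cobb change, which is compared ITT first by t-test and again by ANCOVA in both sets, and the count sits under subgroup analyses. This stands. It limits the reach of the point and rules out any claim that the trial's main comparison is compromised.

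**The PP restriction is explicit for the count alone.** A reader might infer that all analyses of progression are PP-only, since the regression and the chi-square test follow under the same heading. The text does not say so. What is supported is that their set is unstated.

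**Bias is not shown.** A reader might go further and conclude that the progression result is biased, or biased towards one arm. The documents do not support that. They do not say what treatment after weaning consists of, who receives it or how often, nor how wear time relates to progression. Part of the asymmetry follows from the design, since immediate removal leaves no wear time to achieve. Immediate-arm patients who keep bracing might be removed as major deviations or as treated during follow-up, though no sensor is planned to detect them. What remains is exposure to selection bias, which an ITT analysis would largely avoid.

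**The overlap is a wording fault.** A three-way table implies exclusive classes, so rebound was probably meant as a carved-out subtype. That is a fair reading, but the plan does not state it, and it leaves open whether rebound counts as an event in the logistic model. The overlap does not itself create a difference between arms.

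**Conclusion.** The point holds in this limited form, and it should be fixed before analysis. The only progression result with a named analysis set is in a population selected after randomisation, by rules that differ between arms. Under no true effect and the assumptions above, the one-arm wear-time rule alone moves the PP difference by anything from 0 to 13 points. Unequal removal of treated progressors (30% against 10%) moves it by about 6 points either way. Both effects vanish if exclusion is unrelated to progression. The non-compliance shares, risk ratios, treatment shares and prebrace distribution are all assumed, so these are ranges of what could happen and not estimates of bias.

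The overlap of rebound with progression follows from the text alone and needs no assumption; only its numerical effect does. The ITT-first analysis of Cobb change is untouched.

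**What to change.** - Report and test progression (more than 5 degrees from weaning) by allocated arm in the ITT set at 12 and 24 months, with PP as supportive only. The 12-month time matches the protocol's primary end point.
- Use the ITT set for the logistic regression and the chi-square test, and say so.
- Keep patients treated after weaning in the ITT analysis with their measured angles. Add a sensitivity analysis that counts them as progressed. This should not be the main rule, because the decision to treat is made in an open-label trial.
- Define three exclusive and exhaustive classes. No progression: an increase of 5 degrees or less from weaning. Rebound: an increase of more than 5 degrees with the follow-up angle at or below the prebrace angle. Progression: an increase of more than 5 degrees with the follow-up angle above the prebrace angle. The 32/30/36 patient above then falls in progression only.
- State that the logistic outcome is any increase of more than 5 degrees, so it combines the last two classes.
- Add the prebrace Cobb angle to the data list.

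The cost is SAP wording, one extra analysis, retrieval of one value per patient from existing clinic records, and less prominence for the PP result. The SAP's ITT set still omits patients without a measurement, so the numbers missing should be shown by arm.
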